Health status	HF registry	T0, T1*, T2	SF-36 or SF-12 questionnaire (subset of SF-36)^54^: a validated patient-reported survey of patient health. Both questionnaires consist of eight sections with scores: vitality, physical functioning, bodily pain, general health perceptions, physical role functioning, emotional role functioning, social role functioning and mental health. Each score is transformed into a scale of 0–100 on the assumption that each question carries equal weight. The lower the score, the more disability.
Health-related quality of life	HF registry	T0, T1*, T2	SF-36 or SF-12 questionnaire. QALY will be calculated based on the SF-6D, a model in which a single, preference-based score can be directly calculated for the SF-36 and SF-12.^55^ Scores range from 0.0 (worst health state) to 1.0 (best health state).
Healthcare utilisation	External data source, EHR	T1, T2	Healthcare utilisation based on (1) the number of outpatient visits, plus (2) the number of visits to the general practice related to HF.

*The HF registry collects data standard at baseline (T0), after 6 months (T1) and after 12 months (T2). The RELEASE-HF study conforms to the timeframes of the HF registry. Therefore, data will be collected at 6 months, although the outcome measurements are after 12 months.

†The HF registry defines telemedicine as telemonitoring.

EHR, electronic health record; GP, general practitioner; HF, heart failure; ICD, implantable cardioverter defibrillator; NYHA, New York Heart Association; QALY, quality-adjusted life year; RELEASE-HF, REsponsible roLl-out of E-heAlth through Systematic Evaluation – Heart Failure; SF-12, 12-item short form health survey; SF-36, 36-item short form health survey; SF-6D, six-dimensional health state short form.

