The primary outcome model is a linear mixed model with a random intercept for the participating centre and is specified as follows. The outcome is measured in days, and because the final measurement may be less or more than 365 days after baseline, we rescale the number of days of unplanned hospitalisation to the number of days under follow-up to 365 days. The outcome is computed by subtracting the days of unplanned hospitalisation or death from 365. The earlier described confounding variables are added to the primary outcome model to adjust for confounding. Continuous covariates are modelled using splines. Multicollinearity between confounding variables and the telemedicine status is evaluated. The coefficient for telemedicine in the primary outcome model represents the average treatment effect of offering any telemedicine within 3 months after HF diagnosis compared with not offering telemedicine on days with unplanned HF-related hospitalisation during a year in the population of patients with newly diagnosed HF. Robust SEs are estimated to compute CIs.

For the secondary outcome functional status, a similar approach is taken to estimate the average treatment effect of offering any telemedicine within 3 months after HF diagnosis compared with not offering telemedicine on functional status after 1 year in the population of patients with newly diagnosed HF. For this analysis, the outcome model is a multinomial regression model, and baseline functional status is added as a covariate. The risk difference relative to the reference outcome category is assessed using the predicted outcomes of the primary outcome model offering of telemedicine versus not offering, to obtain the marginal risk difference.^38–40^ Similarly, for the secondary outcomes health status and hrQoL, the outcome model is a probit regression model, with baseline measurements added as a covariate. Healthcare utilisation will be assessed using a Poisson regression model, and all-cause mortality will be assessed using binary logistic regression.

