##### Research question 1: effectiveness of telemedicine in patient subgroups

Research question 1 investigates the effectiveness of telemedicine across subgroups of patients with HF. Patient-related subgroups were identified by a systematic literature review of randomised controlled trials (RCTs) of telemedicine: age, severity of HF (NYHA class at baseline), sex, SES, presence of depression, atrial fibrillation and type of HF (HF with preserved ejection fraction (HFpEF), HF with midrange ejection fraction (HFmrEF), HF with reduced ejection fraction (HFrEF)) (table 3).^20–24 41–49^ Stratified analyses of the primary outcome model are performed to estimate the above-defined average treatment effect in each of the subgroups. Heterogeneity in telemedicine effect across age is assessed on a continuous scale, where an interaction between age and telemedicine status is added to the primary outcome model, and the expected number of days out of hospital across age ranges from 50 to 90 years is predicted from this model under telemedicine offered versus not offered.

In an additional analysis, heterogeneity across time since diagnosis is explored for the entire cohort, without restricting to patients with a maximum of 3 months since HF diagnosis at baseline (diagnosed ≤3 months before baseline compared with >3 months before baseline).

The secondary outcomes functional status, health status and hrQoL are assessed using similar approaches but using multinomial, probit and probit regression model, respectively. Healthcare utilisation will be assessed using a Poisson regression model, and all-cause mortality will be assessed using binary logistic regression.

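### Health status and hrQoL are defined as 0–100 and 0–1 scores but assigned an unqualified probit model, so their analysis and effect measure are undefined; the NYHA risk difference also cites the wrong model by name

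*Protocol article*

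**What the plan says.** **Outcome scales (Table 1).** For the eight SF-36/SF-12 section scores that make up health status: "Each score is transformed into a scale of 0–100 on the assumption that each question carries equal weight". For hrQoL, a single SF-6D value: "Scores range from 0.0 (worst health state) to 1.0 (best health state". Neither row gives a responder definition, a threshold or a set of ordered categories.

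**Models (Preparation of the statistical model).** The overall analysis states: "for the secondary outcomes health status and hrQoL, the outcome model is a probit regression model", with the baseline value as a covariate. The subgroup section (research question 1) says that functional status, health status and hrQoL are "assessed using similar approaches but using multinomial, probit and probit regression model, respectively". The component section (research question 2) uses the same words.

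**NYHA.** Functional status receives its own multinomial model with baseline class as a covariate. The marginal risk difference is then said to be obtained "using the predicted outcomes of the primary outcome model offering of telemedicine versus not offering". Earlier in the same section that term is defined: "The primary outcome model is a linear mixed model with a random intercept for the participating centre". Its outcome is days.

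**The concern.** A model has been stated, and it does not fit the outcomes the article itself defines. This differs from leaving detail to an analysis plan. The other outcomes in the same section have models that suit their scale: linear for days, multinomial for NYHA class, Poisson for healthcare utilisation, binary logistic for death. Health status and hrQoL stand out, and because the mismatch appears in three sections, a single typing error is unlikely.

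An analyst following the text cannot tell what is to be reported for these two outcomes. It could be a difference in mean score, a difference in the probability of passing some threshold, or a coefficient on a latent scale. If the gap were filled by choosing a threshold, that choice could be made after seeing the data. It would recur for eight section scores and again in each subgroup and component analysis.

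**Working it through.** No figure in the article bears on this point, so the check sets outcome scale against model. The sample size rests on days only (432 × 12 = 5184; 5184 / 0.8 = 6480) and does not enter.

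**Step 1: outcome against model**

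| Outcome | Scale in the article | Model in the article | Match |
|---|---|---|---|
| Days alive without unplanned hospitalisation | days | linear mixed | yes |
| Functional status | four NYHA classes | multinomial | yes |
| Health status | eight scores, 0–100 | probit | no |
| hrQoL | SF-6D, 0.0–1.0 | probit | no |
| Healthcare utilisation | visit counts | Poisson | yes |
| All-cause mortality | yes/no | binary logistic | yes |

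Costs, the sixth secondary outcome, are handled in the cost-effectiveness section.

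**Step 2: illustration on one simulated data set.** All inputs are assumptions, since the article gives no distribution for these scores: N = 2000, baseline score normal (mean 50, SD 20), outcome = 10 + 0.7 × baseline + 3 × telemedicine + error (SD 15), limited to 0–100.

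- A standard binary probit routine refuses the 0–100 score, and also refuses the score divided by 100.
- A linear model with baseline score gives 3.54 points (SE 0.667, z = 5.3).
- Probit after a split gives:

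| Cut-off | Coefficient | SE | z |
|---|---|---|---|
| 40 | 0.20 | 0.065 | 3.0 |
| 50 | 0.28 | 0.064 | 4.3 |
| 60 | 0.33 | 0.071 | 4.6 |

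**Step 3: what the illustration shows.**

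- *Precision.* On the scale of the error SD, the linear model's SE is 0.667 / 15 = 0.044. The probit SEs are larger by factors of 0.064 / 0.044 ≈ 1.4 to 0.071 / 0.044 ≈ 1.6. Splitting costs precision at every cut-off tried.
- *Dependence on the cut-off.* In this set-up the true probit coefficient is 3 / 15 = 0.20 at every cut-off, so the spread from 0.20 to 0.33 is chance. It still shows how far the reported result can move with a cut-off picked after the fact. A risk difference also changes systematically. Ignoring the limits at 0 and 100, the outcome means are 10 + 0.7 × 50 = 45 and 48, with SD √((0.7 × 20)² + 15²) = 20.5. The difference in the probability of reaching the cut-off is then 0.652 − 0.596 = 5.5 percentage points at 40, 0.461 − 0.404 = 5.7 at 50, 0.279 − 0.232 = 4.7 at 60, and 0.059 − 0.044 = 1.5 at 80. The same 3-point effect thus yields different answers according to a number the article does not give.

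**Step 4: NYHA.** A linear model for days predicts expected days. It has no outcome categories and hence no reference category, so no NYHA risk difference can be computed from it. The multinomial model named in the preceding sentence does give class probabilities.

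**The case against.** **Probit need not mean binary probit.** Fractional probit handles a 0–1 score, or a 0–100 score divided by 100, and ordered probit handles ordered categories. Neither needs a cut-off. The same section writes binary logistic for mortality and does not write binary before probit. This stands in part. A reader might infer that the model can never be run, or that it forces a split; that is true only of ordinary binary probit. But the article names no variant, gives no categories and states no effect measure, and the unqualified term ordinarily means the binary model. The text cannot be followed until one is named.

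**The cost-effectiveness analysis is untouched.** This stands. A reader might infer that probit deprives that analysis of its mean utility difference. The Cost-effectiveness section takes utilities and QALYs directly from average hrQoL scores and does not use the probit model.

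**The loss cannot be sized from the documents.** This stands. A reader might quote the textbook result that a median split of a normal score keeps 2/π = 64% of the information. The article plans no median split, nor any other, and gives no distribution for the scores. That figure is not a consequence of this plan.

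**The NYHA wording is a slip.** This stands too. The preceding sentence names the multinomial model, and only that model has a reference category. It is a correction to make and no evidence of a wrong analysis.

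**A journal article may leave the variant to the analysis plan.** It may omit a model, but here it states one, three times, that does not match its own outcome definitions.

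**Conclusion.** The point holds for health status and hrQoL, two of the six secondary outcomes. As written, each has an unqualified probit model set against a bounded score with no cut-off or categories, so neither has an executable prespecified analysis or a defined effect measure. This applies to the overall analysis and to research questions 1 and 2. It rests on reading probit in its usual sense, as a model for a binary outcome; a named fractional or ordered variant would resolve it.

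Dichotomising would lose precision and tie the result to an unstated cut-off. The simulated figures show the direction of that harm under assumed data and do not measure its size in this study.

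The NYHA reference is literally wrong and carries little weight. The primary outcome, its model, the subgroup analyses of days, the sample size and the cost-effectiveness calculation do not change.

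**What to change.** 1. In Preparation of the statistical model, Research question 1 and Research question 2, replace probit for health status and hrQoL with a linear mixed model: random intercept for centre, the same confounders, baseline score as covariate, robust SEs. Report the adjusted mean difference for each of the eight section scores and for SF-6D.
2. If a fractional or ordered probit was intended, name it in all three places, with the rescaling or categories used and the effect measure to be reported. If a true binary outcome was intended, state the cut-off and its justification before the data are analysed.
3. In Preparation of the statistical model, say that the NYHA marginal risk difference comes from the multinomial model's predicted class probabilities, averaged with telemedicine offered and not offered.

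The cost is one wording change in three sections and one further sentence for NYHA, with any separate analysis plan brought into line. No new data are needed, and the linear model reuses the structure already set up for the primary outcome.

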#### Secondary outcomes

The secondary outcomes are all-cause mortality, functional status, health status, health-related quality of life (hrQoL), healthcare utilisation within 1 year of follow-up and costs of care (table 1).

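### The visit counts are given a Poisson model with no dispersion term, robust variance or centre effect attached, so its intervals may be too narrow, most of all for the hospital-level component contrasts

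*Protocol article*

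**What the plan says.** Table 1 of the protocol article defines the outcome as "Healthcare utilisation based on (1) the number of outpatient visits, plus (2) the number of visits to the general practice related to HF", with the source given as "External data source, EHR". The Secondary outcomes section places it in a one-year window: "healthcare utilisation within 1 year of follow-up and costs of care".

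The subsection on preparation of the statistical model assigns the method: "Healthcare utilisation will be assessed using a Poisson regression model". The sections on research questions 1 and 2 name the same model again. None of the three places adds a dispersion parameter, a centre term, a variance estimator or an exposure time.

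The paragraph on the primary outcome in that subsection is more detailed. It specifies a linear mixed model with a centre random intercept, rescales for unequal follow-up ("because the final measurement may be less or more than 365 days after baseline, we rescale the number of days of unplanned hospitalisation"), deals with death ("The outcome is computed by subtracting the days of unplanned hospitalisation or death from 365") and ends with "Robust SEs are estimated to compute CIs". The next paragraph carries this approach over to functional status, and then to health status and quality of life. Utilisation and mortality follow in a separate sentence without that link. The sections on research questions 1 and 2 keep the same split.

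**The concern.** A Poisson likelihood fixes the variance at the mean. Visit counts pooled across NYHA classes and at least 29 hospitals will probably vary more than that, even after adjustment. If so, model-based SEs are too small and chance differences look significant.

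Research question 2 is the most exposed. There, the presence of a service centre, an educational module or a high-intensity protocol is a property of the hospital, so the contrast is made between hospitals. A model without a centre term counts patients of one hospital as independent evidence about that hospital's component.

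Utilisation is analysed overall, by subgroup and by component. A false difference in visits would be read as a workload effect of telemedicine or of one of its components.

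**Working it through.** **No figure to reproduce.** The article gives no mean, variance or sample-size figure for visits. All inputs below are assumptions, shown as ranges.

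**1. Overdispersion.** For a negative binomial count with mean μ and dispersion k, the variance divided by the mean is 1 + kμ. The true SE exceeds the model-based Poisson SE by √(1 + kμ). The actual type I error of a nominal 5% test is 2[1 − Φ(1.96/√(1 + kμ))].

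| μ (visits/year) | k | Variance/mean | SE ratio | Type I error |
|---|---|---|---|---|
| 4 | 0.3 | 1 + 1.2 = 2.2 | 1.48 | 0.186 |
| 10 | 0.5 | 1 + 5.0 = 6.0 | 2.45 | 0.424 |

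Over a wider range (μ 2 to 8, k 0.2 to 1.0), the SE ratio runs from 1.18 to 3.0 and coverage of a nominal 95% interval from 90% down to 49%. Here k means dispersion left after covariate adjustment.

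**2. Does a robust variance repair it?** A simulation used 400 runs, 2000 patients, μ = 4, k = 0.5, follow-up of 365 days with SD 30, 10% deaths in both groups, a true rate ratio of 1 and no clustering. Poisson without an offset gave a rate ratio of 0.998. Coverage was 73.8% with model-based SEs and 96.0% with robust SEs. The Poisson mean model is therefore not the fault; the variance is what matters.

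**3. Clustering in research question 2.** Assume m = 50 telemedicine patients per hospital and an intraclass correlation (ICC) of 0.01 to 0.05. The design effect is 1 + (m − 1) × ICC.

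- ICC 0.01: 1 + 49 × 0.01 = 1.49, type I error 2[1 − Φ(1.96/√1.49)] = 0.11.
- ICC 0.05: 1 + 49 × 0.05 = 3.45, type I error 2[1 − Φ(1.96/√3.45)] = 0.29.

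This is from clustering alone and comes on top of step 1. Robust SEs computed patient by patient would not remove it.

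**4. Exposure time.** The same simulation was rerun with unequal deaths and no true effect.

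| Deaths, no telemedicine vs telemedicine | Rate ratio, no offset | Rate ratio, offset |
|---|---|---|
| 10% vs 10% | 0.998 | 0.998 |
| 12% vs 8% | 1.023 | 1.001 |
| 15% vs 5% | 1.054 | 1.000 |

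A hand check agrees. If deaths are spread evenly over the year, a death rate d leaves mean time 1 − d/2, so the ratios are 0.96/0.94 = 1.021 and 0.975/0.925 = 1.054. The shift is a few per cent, and only when mortality differs between groups.

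**The case against.** The strongest reply is that a journal article names the model family and leaves dispersion, variance estimation and offsets to an analysis plan that is not shown. Nothing in the article rules out robust SEs for the Poisson model, and they appear in the same subsection. This stands in part: too-narrow intervals follow only if model-based SEs are used, and the article does not say that they are. But the text names the Poisson model three times, attaches the protective features to the primary model, and extends that approach by name to other secondary outcomes only. Even a carry-over of robust SEs would not settle research question 2 unless they are clustered by centre.

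Three stronger readings are tempting, and the documents do not support them.

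- **That the counts are known to be overdispersed.** No visit mean or variance is given, and the long list of baseline confounders would absorb some of the variation. Overdispersion is an expectation.
- **That late final visits bias the visit ratio.** The statement that "the final measurement may be less or more than 365 days after baseline" concerns registry hospital days. Visits come from external data and the electronic record over one year, so they need not depend on the date of the last registry visit.
- **That the estimate is wrong because early deaths count as low use.** Telemedicine status is read at 6 months, so a patient who dies at month 2 may belong to neither group. With balanced mortality there is no bias. Total visits in one year is also a legitimate target for a workload question, and an offset changes that target to visits per day alive.

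**Conclusion.** The point holds for variance and clustering. As named, the Poisson model has nothing attached that allows for extra variation or for hospitals. If it is fitted with model-based SEs, the SEs would be too small by a factor of about 1.5 to 2.4 and the type I error would be about 19% to 42%, for an assumed mean of 4 to 10 visits and a dispersion of 0.3 to 0.5. The figures fall if robust SEs were intended or if covariates explain part of the dispersion. For the component contrasts, clustering alone would bring the error to about 11% to 29% under the assumed hospital size and ICC.

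Exposure time is a lesser matter: a shift of about 2% to 5% under assumed unequal mortality, and none when mortality is balanced. A reader should not conclude that the effect estimate is wrong.

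This is a secondary outcome, and the primary analysis and the sample size are unaffected. It is still worth changing, because a better-specified method is available at almost no cost.

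**What to change.** For healthcare utilisation in the overall, research question 1 and research question 2 analyses, specify one of the following:

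- a negative binomial model with a centre random intercept; or
- a Poisson model with robust SEs clustered by centre.

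State that visits are counted over a fixed one-year window from baseline. Add a sensitivity analysis with the log of days alive under follow-up as an offset, and say that it estimates visits per day alive, not total visits.

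The cost is a line or two of wording and wider intervals, mainly in research question 2. No new data and no change in sample size are needed.

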### Outcome measures

#### Primary outcome

The number of days alive without unplanned hospitalisation within 1 year of follow-up is derived from the number of unplanned hospital days as collected in the HF registry (table 1).

**Table 1 T1:** Operationalisation of exposure variable and study outcomes

Variable	Source	Time of collection	Operationalisation
Exposure			
Telemedicine	HF registry, telemedicine-generated data	T0, T1*, T2	Whether a patient receives telemedicine. Five categories: (1) no telemonitoring†; (2) telemonitoring by telephone; (3) telemonitoring, non-invasive based on traditional parameters (eg, blood pressure, ECG); (4) telemonitoring using ICD based on HF parameters; and (5) telemonitoring, invasive using sensors in the bloodstream or heart.
Primary outcome			
Number of days spent alive without unplanned hospitalisations within 1 year of follow-up	HF registry	T1*, T2	Number of days directly related to unplanned cardiac hospital admission due to HF. Number of admission days will be summed up over a period between follow-up moments and subtracted from 365 days.
Secondary outcomes			
Costs	Derived from HF registry, external data source, EHR, interviews	T0, T1*, T2	Costs estimated from patient, disease and treatment characteristics. Information taken into account includes medication use, whether the patient underwent cardiac interventions (eg, pacemaker implantation, percutaneous coronary intervention), use of telemedicine, hospital admission days, visits to the outpatient clinic, visits to the emergency room, admission days at an intensive care unit and visits to the GP related to HF.
All-cause mortality	HF registry, external data source	T1*, T2	Mortality status, determined after verification at the Personal Records Database (in Dutch: Basisregistratie Personen). Mortality is independent of HF (all-cause).
Functional status	HF registry	T0, T1*, T2	NYHA classification: a functional classification of patients based on severity of symptoms and physical activity, with specific attention to fatigue, palpitation and dyspnoea. Scores are linked to one of four NYHA classes: class I: no limitation; class II: slight limitation; class III: marked limitation; and class IV: unable to carry on any physical activity without discomfort.^1^

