We plan to perform the following additional analyses. First, we plan to perform the analysis with the start of follow-up defined at the T1 (after 6 months) measurement and the outcome of unplanned hospitalisation days during 6 months. This is because telemedicine status can be misclassified when it is started shortly after baseline but is not registered in the data. Second, we plan to perform a per-protocol analysis of telemedicine use if detailed information on starting and stopping of telemedicine is available through linkage. Finally, we plan to perform all analyses in the entire cohort, rather than the cohort restricted on HF diagnosis, to a maximum of 3 months prior to T0 (baseline).

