##### Research question 2: effectiveness of different telemedicine components

Research question 2 investigates the effectiveness of the different forms of telemedicine intervention. We assess this question by performing three separate analyses in which intervention aspects are contrasted in the subset of participants that received telemedicine. The presence or absence of a telemedicine component is determined at a hospital level. The components of telemedicine that are contrasted are presence versus absence of a service centre, presence versus absence of an educational module, and high-intensity versus low-intensity protocol (table 2).

The population of interest is patients with newly diagnosed HF (maximum 3 months prior to baseline) who received telemedicine. Offering of telemedicine is measured at 6 months after baseline.

In addition to the set of confounding variables at the patient level used in the analysis above, confounding variables at the hospital level are considered because indication for telemedicine is expected to differ across hospitals. Confounding variables include academic or non-academic hospital, presence of a specialised heart centre, presence of an outpatient ward, size of outpatient ward (number of patients/year), staffing of the HF outpatient clinic and full-time equivalent of outpatient-ward staff.

For each of the three contrasts, the primary outcome model is fitted to estimate the average treatment effect of a component relative to the corresponding reference component on days of unplanned hospitalisation during 1 year in the population of patients with newly diagnosed HF that initiated telemedicine.

The secondary outcomes functional status, health status and hrQoL are assessed using similar approaches but using multinomial, probit and probit regression model, respectively. Healthcare utilisation and all-cause mortality will be assessed using Poisson regression model and binary logistic regression, respectively.

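### As worded, the 6-month landmark analysis counts only hospital days and not days lost to death, so it does not cleanly check the primary result

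*Protocol article*

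**What the plan says.** All references are to the Protocol article.

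- **Primary outcome, scoring rule** (Preparation of the statistical model): "The outcome is computed by subtracting the days of unplanned hospitalisation or death from 365". Days dead count as days lost. Hospital days are also rescaled for unequal follow-up: "we rescale the number of days of unplanned hospitalisation to the number of days under follow-up to 365 days".
- **First additional analysis** (same section): to be done "with the start of follow-up defined at the T1 (after 6 months) measurement and the outcome of unplanned hospitalisation days during 6 months". The reason given is "This is because telemedicine status can be misclassified when it is started shortly after baseline but is not registered in the data". No reason is given for a different outcome.
- **Primary outcome, name and Table 1** (Primary outcome): "The number of days alive without unplanned hospitalisation within 1 year of follow-up is derived from the number of unplanned hospital days", and in the table "Number of admission days will be summed up over a period between follow-up moments and subtracted from 365 days". The name includes being alive; the operationalisation mentions admission days only.
- **Description of the primary coefficient** (Preparation of the statistical model): an effect "on days with unplanned HF-related hospitalisation during a year in the population of patients with newly diagnosed HF".
- **Research question 2**, which fits the primary outcome model: an effect "on days of unplanned hospitalisation during 1 year in the population of patients with newly diagnosed HF that initiated telemedicine".

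**The concern.** In the primary analysis, telemedicine status for the whole year is taken from the 6-month measurement, halfway through the period over which the outcome accrues. The landmark analysis moves the start of follow-up to T1, so that exposure is known before outcome time begins. That makes it a useful check on exposure timing, and it does not depend on linkage.

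The stated purpose justifies a later start. It does not justify leaving out death. If the outcome is hospital days alone, time dead is treated as time without admission, and longer survival gives more time in which to be admitted. A benefit of telemedicine on survival after month 6 would then show as no effect, or as a very small effect in the wrong direction. A reader comparing the landmark result with the primary result could not tell how much of any difference came from the exposure timing that the analysis was meant to examine.

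**Working it through.** **The plan's own figures.** The point disputes no stated number, but the planning effect serves as a yardstick. With a difference of 6.4 days, SD 21.1, 5% type I error (two-sided assumed) and 80% power, the normal approximation gives 171 per arm, 342 in total, and 342 / 0.8 = 428 after 20% dropout. The t-test version gives 172 per arm and 344 / 0.8 = 430. Both are close to the stated 432. Then 432 × 12 = 5184 and 5184 / 0.8 = 6480, as stated. If the effect accrues proportionally, its 6-month share is 6.4 / 2 = 3.2 days.

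**Inputs for the check.** The window is 365 / 2 = 182.5 days. Mortality and hospital-day rates are assumptions, since the article gives none. Deaths are assumed to be spread evenly over the window.

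**Step 1: one patient.** Take a death out of hospital, with no admission, 5 days after T1.
- Hospital days only: 0 days, the same as 182.5 event-free days.
- Death counted: 5 days alive out of hospital.
- Gap: 182.5 − 5 = 177.5 days.

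The place of death and the rescaling matter. Suppose the rescaling to days under follow-up carries over and follow-up ends at death. A patient who spends all 5 days in hospital and dies there scores 5 / 5 × 182.5 = 182.5 hospital days, the worst value. Two early deaths would then sit at opposite ends of the scale.

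**Step 2: group means.** Let m be 6-month mortality and h the share of living days spent in unplanned hospitalisation.
- Mean days alive: A = 182.5 × (1 − m/2)
- Mean hospital days: h × A
- Mean days alive out of hospital: (1 − h) × A

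One percentage point of mortality is worth 0.01 × 182.5 / 2 = 0.91 days alive, or 0.98 × 0.91 = 0.89 days alive out of hospital at h = 2%.

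| Mortality, no telemedicine vs telemedicine | h, no telemedicine vs telemedicine | Effect, days alive out of hospital | Effect, fewer hospital days only |
|---|---|---|---|
| 3% vs 3% | 3% vs 2% | 1.80 | 1.80 |
| 4% vs 3% | 2% vs 2% | 0.89 | −0.02 |
| 6% vs 4% | 2% vs 2% | 1.79 | −0.04 |
| 8% vs 4% | 2% vs 2% | 3.58 | −0.07 |
| 6% vs 4% | 3% vs 2% | 3.56 | 1.73 |

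With equal mortality the two outcomes agree. With a mortality difference and equal hospital rates, the hospital-days outcome shows essentially nothing. In the last row it shows about half of the effect.

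**Step 3: against the planning effect.** At 4% to 6% mortality, mean days lost to death are 0.04 × 91.25 = 3.65 to 0.06 × 91.25 = 5.48. A 30% relative reduction (assumed) is worth 1.1 to 1.6 days, which is 34% to 51% of 3.2 days.

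**The case against.** The strongest answer is that this is shorthand. The article describes its own death-counting primary model in the same short form, once for the coefficient and again in research question 2, and Table 1 also mentions only admission days. The landmark sentence speaks of performing the analysis, which most naturally means the same analysis with a later start. This stands: a reader might infer a deliberate switch of outcome, and the text does not show one.

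It does not remove the problem. The coefficient sentence and the research question 2 sentence are both tied to the primary outcome model, whose scoring rule counts death. The landmark sentence names its own outcome and window without that tie. A rule that subtracts from 365 cannot be carried unchanged into a 6-month window, so an analyst has to write a new definition, and the only words supplied omit death.

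Three further limits are fair.
- A reader might infer that the landmark is the only analysis that deals with exposure timing. A per-protocol analysis is also planned if linkage supplies start and stop information, and Data collection and quality control says that the start date of telemedicine is to be collected at patient level.
- A reader might infer that every early death scores as a success. That holds for deaths out of hospital without admission; otherwise it depends on the place of death and on the rescaling.
- A reader might infer that the analysis cannot check the primary result at all. It still tests the hospitalisation component, and it agrees with the composite when mortality is equal. All-cause mortality is modelled separately, although no landmark version is stated.

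Finally, an article may leave the detailed scoring of a sensitivity analysis to the analysis plan. Here, however, the article states an outcome rather than leaving it open, and the outcome it states does not match the primary one.

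**Conclusion.** The point holds as a mismatch in stated outcomes. Followed literally, the landmark analysis leaves out days lost to death, gives some early deaths the best score, and misses about 0.9 days per percentage point of mortality difference over 182.5 days. That figure rests on evenly spread deaths. The 4% to 6% mortality and the 30% reduction used to compare it with the planning effect are assumptions, not figures from the article.

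A disagreement with the primary result could then reflect the dropped deaths together with the later time origin, the shorter window and the restriction to T1 survivors. The last three come with any landmark analysis and would remain after the correction; the first is avoidable. The analysis is therefore informative on hospitalisation but not a clean check of the primary result. Intent to change the outcome is not established. Because this is an additional analysis, the primary result itself is not affected. The change should be made, and it matters more than a point of style because the stated rule gives a worse sensitivity analysis if it is applied as written.

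**What to change.** In the additional-analyses paragraph of Preparation of the statistical model, define the landmark outcome as days alive without unplanned hospitalisation over the 6 months from T1, in patients alive at T1: window length, minus unplanned hospital days, minus days dead. Use the same hospitalisation definition as the primary outcome, and say how the rescaling treats a patient who dies within the window.

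Align the outcome wording in three other places so that each names the same death-counting outcome: the Table 1 operationalisation, the description of the primary coefficient, and the research question 2 effect.

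The cost is one clause and three wording edits. No new data are needed: Table 1 says mortality status is verified against the national personal records database, and the Clinical effectiveness section already plans to report time until death. No sample size figure changes.
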